### Interventions

Both the intervention and control groups will receive routine school-based education from each included preschool plus the app-based education programs. Routine school-based education encompasses health education, including injury prevention, that is performed by preschool teachers. This education is typically based on the suggested course from the Ministry of Education of China and influenced somewhat by the teacher’s knowledge and preferences for teaching injury prevention to children.

The basic framework for child unintentional injury prevention in the app is based on previous theories and research [32]. It comprises four active modules: (1) content learning, including a series of instructional materials to impart basic and practical knowledge and skills; (2) social interaction, consisting of an online forum, online expert consultation opportunities, and locations for users to leave comments that facilitate communication among users and between users and experts; (3) survey and feedback, used for online survey data collection and user’s suggestions, and for experts to reply to user queries; and (4) a personalizing module, allowing users to customize the color scheme of their app and to display the user’s personal learning progress. The four active modules will be identical for both groups during the program and are detailed along with the app design and other functions in a previous publication [32].

The intervention will differ between the intervention and control groups based on the learning contents they receive. The control group will receive a parenting health education program covering topics like pediatric disease risks, childhood nutrition, early childhood development, and child health care. It will exclude any explicit information about unintentional child injury prevention. The intervention group will receive all contents the control group receives plus additional components focused on prevention of common child unintentional injuries in rural areas (e.g., road traffic injury, falls, drowning, suffocation, poisoning, burning, scalding, electric current burns, and other injuries caused by animate or inanimate mechanical forces).

A previous report evaluated a precursor version of this app that was created for urban caregivers [24]. The app has been optimized and refined substantially for this trial to focus on the characteristics and needs of children and families in rural China and to overcome some deficiencies identified in the previous trial. The following specific changes were made:
Enriched and updated the scenarios of knowledge segments tailored to common situations in rural areas of China;increased number and diversified categories of audio recordings (30% vs. 0% of contents in current vs. previous app version), interactive games (20% vs. 3%), cartoons (10% vs. 5%), and videos (10% vs. 6%);reduced proportion of short essays with pictures (30% vs. 86%), based on user’s feedback;increased frequency of dissemination of knowledge segments from 4 times a week to 7 times a week for both groups;introduction of new learning approaches (e.g., audio learning and regular online theme activities via the app forum); andimproved user experience and motivation through upgraded strategies for this app, such as additional online video instruction for using the app, automatic display and interaction with the banner and recommended readings in the app’s homepage, refining online expert consultation and customer service, publishing comments and displaying other users’ comments, and changing the font color in the forum to reduce eye strain.

In addition, the time period of this intervention study will be prolonged for 18 months to demonstrate its long-term effectiveness in reducing injury incidence rate. The previous trial for urban families lasted just 6 months.

All components of the app will be available throughout the study period, ensuring that all users in both groups can retrieve and learn from knowledge segments freely and repeatedly. Except for the differences in the content of the app, the implementation of the app-based intervention will be identical for both groups.

### Strategies to enhance engagement

In order to enhance engagement with the app-based intervention, we will adopt an external support strategy. Specifically, with the support of local partners including the local education bureau, health committee, maternal and child health hospital, centers for disease control and prevention, a coordinating group will be established for each enrolled preschool. The coordinating group that is composed of local office staff members of the charitable foundation “World Vision”, class teachers, and school staffs of each enrolled preschool, will help study participants solve problems with app use and encourage engagement in the study.

Besides sufficient external support from the coordinating groups, several other strategies will be flexibly implemented to encourage active use of the app and participation in the study. First, in both intervention and control groups, a small amount of app-based reward points will be granted based on the participant’s engagement. The reward points will be exchanged for small gifts such as gift cards to refill mobile phone and data services. Second, participants who log in the app for 7 consecutive days will gain a chance to enter a lottery and win additional reward points. Third, we will provide a small gift to students monthly if their caregivers rank among the top 30 active learners over the past month. Finally, automated reminders will be sent to caregivers if they do not read app-delivered knowledge segments or fail to accomplish online questionnaires. If automated reminders fail, the coordinating group will take other actions to remind the participants such as sending a text or voice message or making a phone call.

### Outcome measure

The primary outcome measure will be the incidence rate of unintentional injury among preschoolers in the past 18 months, which will be calculated by combining data from the six follow-up evaluations accumulatively. We will conduct follow-up evaluations on a quarterly basis (every 3 months) to reduce recall bias in participants remembering children’s minor or moderate injuries [24].

An injury event will be included if it meets any of three criteria [24]: (1) child receives a medical diagnosis or treatment by a doctor or other medical professional following an injury; (2) child receives first aid, takes any injury-related medication, or receives massage or cold/hot compress by a family member, teacher or other non-medical staff following an injury; or (3) child is restricted from school or other activities, or is kept in bed or rest for more than a half-day following an injury. If a caregiver reports that a child experienced more than one unintentional injury event in the past 3 months, we will record the number of injury events but collect specific information only about the most serious one.

Unintentional injury incidence rate will be calculated as “number of preschoolers newly experiencing unintentional injury events divided by total number of preschoolers×100%”.

We also will consider several secondary outcome measures, including: (1) the caregiver’s attitudes toward child unintentional injury prevention, (2) caregiver-reported supervision behaviors related to child unintentional injury prevention in the last week, and (3) the caregiver-reported home environment safety based on a standardized audit checklist over the last week. All secondary outcome measures are based on previously-published and validated items [24, 33–36]. Table 1 lists all planned survey items, with the final survey questionnaire to be refined through a pilot survey, as detailed below.

**Table 1 Tab1:** Survey items assessing child caregiver’s attitudes, supervising behaviors, and child home environment safety

**1. Caregiver’s attitudes** (with four response options: completely agree, partly agree, not sure, and completely disagree)	
a. Preventability of preschooler unintentional injury	
b. Self-efficacy to keep child safe from unintentional injury	
c. Necessity of preventing unintentional injury	
**2. Caregiver’s supervising behavior** (with five response options: always, often, seldom, never, and not applicable)	

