### Participant recruitment

Eligible participants meet the criteria: being the primary caregiver of a preschooler attending the included schools.

Potential participants will be excluded from this study if they meet any of the following criteria: (1) unwilling to participate in this study; (2) do not own a smartphone or cannot operate the app independently; (3) cannot read text messages; or (4) expect to move to another city with their children during the study time period. If an eligible caregiver care for more than one eligible preschooler, we will enroll only the youngest child.

In coordination with local cooperative partners (governmental departments and agencies), we will recruit class teachers and school staffs to help coordinate recruitment of study participants in each selected preschool. Those individuals will inform eligible caregivers about the study via multiple existing preschool-family communication channels, such as social media platforms (WeChat or QQ), school apps, printed briefing materials and oral notification. Caregivers who agree to participate will be provided an invitation letter that includes the benefits and responsibilities of participating in this study and instructions to download, install, sign up, log in and use the randomly-assigned app. Moreover, all caregivers who agree to participate will receive a short online guidance video that detailedly introduces basic information about the study and educates the participants on how to utilize the app.

When participants log into the app for the first time, they will be invited to complete and submit the informed consent documentation online. All consenting participants will then complete the baseline survey, which collects information about unintentional injuries the child experienced in the past 3 months as well as information on socio-demographic characteristics, caregiver’s attitudes, caregiver-reported behaviors surrounding child unintentional injury prevention, and caregiver-reported home environment safety based on the standardized safety checklist over the prior week.

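### The three-month look-back is not tied to the previous survey, so unequal response delays leave parts of the 18-month primary outcome period that no survey asks about

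*Protocol article*

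**What the plan says.** Under Outcome measure, the protocol article defines the primary outcome as injury incidence over 18 months, "which will be calculated by combining data from the six follow-up evaluations accumulatively". The spacing is explained there: "We will conduct follow-up evaluations on a quarterly basis (every 3 months) to reduce recall bias". The incidence is a per-child proportion: children with a new injury event divided by all children.

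The only recall period given for injuries is three months. At baseline (Participant recruitment) the survey collects "information about unintentional injuries the child experienced in the past 3 months". At follow-up it appears in the rule for multiple events: "If a caregiver reports that a child experienced more than one unintentional injury event in the past 3 months", then "we will record the number of injury events but collect specific information only about the most serious one".

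Late completion is provided for. Under Strategies to enhance engagement, "automated reminders will be sent to caregivers if they do not read app-delivered knowledge segments or fail to accomplish online questionnaires", and then "If automated reminders fail, the coordinating group will take other actions to remind the participants", by message or call. Collection of formal data adds a phone interview where needed. The article states no completion window, and it links the look-back neither to the previous survey nor to calendar dates.

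**The concern.** Six three-month look-backs add up to 18 continuous months only if every survey is answered exactly three months after the one before. If one survey is answered on time and the next three weeks late, three weeks fall between the two windows. Injuries in those weeks are never asked about, and an analysis plan cannot restore them. If a late survey is followed by a punctual one, three weeks are asked about twice.

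At stake are the absolute incidence, which would be too low, and some power. The treatment comparison is also at stake if caregivers in one arm answer later than in the other. Surveys are delivered through the app and the app's content differs by arm, so this last possibility cannot be ruled out in advance.

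**Working it through.** **Inputs from the Sample size section:** control risk 30% over 18 months, ratio 0.80 (so 24%), ICC 0.005, 150 children per preschool, attrition 15%, power 80%, alpha 0.05 (two-sided, per Data analysis plan), N = 3508.

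**Assumed, because the article gives no figure:** baseline answered on day 0; surveys due every 91 days (6 × 91 = 546); a 91-day look-back from the day of answering; delays d₁ to d₆ independent; constant injury rate.

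**1. The plan's own figure.** Two proportions, 0.30 against 0.24, need 859 per arm. Design effect = 1 + 149 × 0.005 = 1.745. 859 × 1.745 / 0.85 = 1763.5, rounded up to 1764 per arm, or 3528 in total. With unpooled variance the total is 3514. The stated 3508 is reproduced to within 0.6%. Effective size per arm at N = 3508 is 3508 × 0.85 / 2 / 1.745 = 854, which gives power of 79.8%.

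**2. Window arithmetic.** With d₀ = 0, the gap before survey k is max(dₖ − dₖ₋₁, 0) and the overlap is max(dₖ₋₁ − dₖ, 0). If every delay equals d, the only gap is d days after baseline, there is no overlap, and the last window runs d days past month 18.

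**3. Expected days.** For independent exponential delays with mean m, the first gap averages m and each of the other five averages m/2. Uncovered = m + 5m/2 = 3.5m. Asked twice = 5m/2 = 2.5m. Total days asked about are always 6 × 91 = 546, so distinct days observed = 546 − 2.5m if days after month 18 are counted.

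**4. Observed risk and power.** Control rate = −ln(0.70) = 0.357 per 18 months; intervention rate = −ln(0.76) = 0.274. Observed risk is the mean of 1 − exp(−rate × days observed / 546), from 400,000 simulated children per row. Each cell from control risk onward gives two values: only days up to month 18 counted / later days counted as well.

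| Mean delay | Uncovered days | Asked twice | Control risk | Risk ratio | Power at N = 3508 |
|---|---|---|---|---|---|
| 7 | 24.5 (4.5%) | 17.5 | 28.9% / 29.2% | 0.799 / 0.799 | 78.3% / 78.7% |
| 14 | 49 (9.0%) | 35 | 27.7% / 28.4% | 0.797 / 0.798 | 76.6% / 77.6% |
| 21 | 73.5 (13.5%) | 52.5 | 26.5% / 27.5% | 0.796 / 0.797 | 74.7% / 76.3% |

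Hand check of the first row: 0.357 × 521.5 / 546 = 0.341, and 1 − exp(−0.341) = 28.9%.

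**5. Another delay distribution.** Uniform delays of 0 to 30 days give 40 days uncovered, 25 asked twice, 92.7% of the nominal period covered, control risk 28.2%, ratio 0.798 and power 77.3% (days up to month 18 only).

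**6. Delays that differ by arm.** With no true effect and mean delays of 7 and 14 days, the ratio is 27.7 / 28.9 = 0.96, or 28.4 / 29.2 = 0.97 if days after month 18 count. With the planned effect and the intervention arm answering faster (7 against 14), the observed ratio is 0.82 to 0.83 and power is 60% to 66%. With the arms reversed, the ratio is 0.77 to 0.78.

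**The case against.** The strongest reply is that the article does not show the injury question. The three-month phrase at follow-up sits in a rule about recording multiple events; Table 1 covers only attitudes, supervision and home environment; and the questionnaire is to be finalised after the pilot. The phrase could be shorthand for the quarter being surveyed. This stands as a limit on certainty. It does not remove the point, because the stated recall period is the only one in the article and it fits the outcome only under punctual completion.

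Lateness is also inferred: the article describes how non-completers are chased, not how late they are. Independent delays are an unfavourable assumption, since a caregiver who is always equally late loses only one stretch at the start. Both stand, which is why the sizes above are conditional.

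A reader might infer that overlaps inflate the primary outcome. They do not: a child whose injury is reported twice is still one injured child. Only the recorded number of events can be double-counted.

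A reader might also infer that overlapping reports can never be disentangled. That goes too far. The restriction on detail applies only to windows with more than one event. At the planning rate, the quarterly mean is 0.357 / 6 = 0.0594, so 5.8% of quarters contain an event and 0.17% contain two or more; about 97% of positive reports describe a single event. The article does not list the details collected, so it does not show that dates are absent.

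Finally, anchoring to the last survey lengthens recall, which works against the reason given for quarterly surveys. That cost is real and belongs in the fix.

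**Conclusion.** The concern holds as a modest, correctable weakness in how the primary outcome is collected. Unequal delays between surveys create days that are never asked about. For assumed mean delays of 7 to 21 days, the loss is 24.5 to 73.5 of the nominal 546 days, or a net 17.5 to 52.5 days if days after month 18 are counted. Observed control risk then lies between 29.2% and 26.5% instead of 30%. With equal delays by arm, the ratio barely moves and power falls by about 1 to 3 points at means of 7 to 14 days, and by 3.5 to 5 points at 21 days.

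One could be tempted to conclude that the trial does not measure its 18-month outcome. The figures do not support that: even delays spread over 30 days leave about 93% of the period covered.

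Nor do the documents show a biased comparison. Bias needs delays that differ by arm. The Interventions section describes implementation as the same in both groups apart from app content, and reminders and phone back-up are not distinguished by arm. Differing delays remain possible because app content may affect app use, but the 7-against-14-day example is only an illustration.

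The sample size is unaffected.

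**What to change.** Unless the full questionnaire already does so, replace the three-month look-back in each follow-up survey by *since your last survey on [date shown by the app]*, using the baseline survey date at the first follow-up. Record the date, or at least the month, of every reported event, not only of the most serious one. Count only events up to month 18 in the primary outcome. Gaps and overlaps between completed surveys are then zero by construction, and the design figures stay as they are.

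The change is one of wording and one date field, made before baseline while the questionnaire is still open to revision after the pilot. It costs one extra field for each additional event and longer recall for late responders. After a missed survey the recall period becomes about six months or more, so those reports should be flagged and examined in a sensitivity analysis.

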**2.1 Risky behaviors**	
a. Letting child cross the road alone	
b. Taking child to cross a road at a location without a pedestrian crossing	
c. Letting child swim in a pond or river without adult supervision	
d. Looking left and right before taking child to cross the road	
e. Letting child ride a bicycle or scooter on the road	
f. Holding the child or letting the child sit alone on the front passenger seat when riding in a car	
g. Leaving child playing alone on the bed or stairs	
h. Leaving the child alone for a short time when bathing	
i. Adding hot water when the child is still in the bathtub	
j. Feeding child while the child is playing, laughing, or crying	
k. Giving child a large piece of food, or a whole round food (e.g., grape, nut)	
l. Leaving child at home alone	
m. Leaving the child unattended while the adult is cooking or doing housework	

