**2.2 Safe behaviors**	
a. Using child restraints for child when taking a car	
b. Requiring child to wear safety protective equipment when riding a bicycle or scooter	
c. Testing water temperature before bathing the child	
d. Pouring the water out of the bathtub immediately after using it	
e. Keeping hot substances and lighters out of child’s reach	
f. Keeping sharp objects out of child’s reach	
g. Keeping medicines, detergents, sanitizers, antiseptics, and pesticides out of child’s reach	
h. Keeping small objects out of child’s reach	
**3. Home environment safety** (with six response options: completely like this, mostly like this, partly like this, mostly unlike this, completely unlike this, and not applicable)	

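### Table 1 lists a safe road-crossing behaviour (item 2.1d) under risky behaviours; if items are coded by heading, this item of a secondary outcome is scored backwards

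*Protocol article*

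**What the plan says.** The Outcome measure section of the protocol article names three secondary outcomes. The second is "caregiver-reported supervision behaviors related to child unintentional injury prevention in the last week". Table 1 gives the items behind it in two sublists, "2.1 Risky behaviors" (13 items, a to m) and "2.2 Safe behaviors" (8 items, a to h). One response format covers both: "with five response options: always, often, seldom, never, and not applicable".

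Item d of the risky sublist is "Looking left and right before taking child to cross the road". It is not repeated in the safe sublist.

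Two further statements bear on the point. On the origin of the items, the section says: "All secondary outcome measures are based on previously-published and validated items". On their status, it says: "Table 1 lists all planned survey items, with the final survey questionnaire to be refined through a pilot survey". Neither the Outcome measure section nor the Data analysis plan says how answers become points, which items are reverse-coded, or whether the sublists are summed separately or together.

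**The concern.** On a shared frequency scale, the answer always is the best response to a safe item and the worst response to a risky one. Someone has to tell the analyst which items run which way, and in this article only the sublist headings do so. Item 2.1d has the direction of a safe item and the label of a risky one.

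An analyst who reverse-codes everything under the risky heading would give the caregiver who always looks both ways the worst mark on that item. Road traffic injury is the first example in the list of content that only the intervention group receives (Interventions section), so this is an item on which the intervention arm could plausibly improve. Any such improvement would be subtracted from the supervision outcome instead of added, which pulls a true benefit towards the null.

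**Working it through.** The plan states no figure on this point, so there is none to reproduce. The check has two parts: a reading of the table, and arithmetic for what coding by heading would do.

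**Reading the table**

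- Risky sublist: 13 items. Twelve describe exposing the child to a hazard, such as crossing alone, swimming unsupervised or being left at home alone. Item d describes a precaution.
- Safe sublist: 8 items, all precautions, such as using restraints or testing bath water. Item d is of this kind.
- The home environment items are also split into risky (9) and safe (7). Across the four sublists there are 13 + 8 + 9 + 7 = 37 items. By my reading, 36 agree with their heading and item 2.1d is the only exception. The headings therefore work as direction labels throughout, and this item looks like a slip.

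**Arithmetic under stated assumptions**

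Assumptions, none of which is in the article: the four graded answers score 0 to 3, higher is safer, items under the risky heading are reverse-coded, weights are equal, and nobody answers not applicable.

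1. Effect on the item itself. Moving from never to always should add 3 points. Coded by heading, it subtracts 3.
2. Effect on a sum of k items when every item truly improves by the same amount δ:
   - true change = kδ
   - observed change = (k − 1)δ − δ = (k − 2)δ
   - observed/true = (k − 2)/k
3. For the 2.1 items alone, k = 13: 11/13 = 84.6%.
4. For all behaviour items, k = 13 + 8 = 21: 19/21 = 90.5%.
5. Sensitivity to the equal-improvement assumption. Let item d improve by rδ and each of the other items by δ. Then observed/true = (k − 1 − r)/(k − 1 + r).
   - r = 0 (no effect on item d): ratio 1, no distortion of the change.
   - r = 1: the 84.6% and 90.5% above.
   - r = 2 (illustrative): (12 − 2)/(12 + 2) = 10/14 = 71.4% for k = 13, and (20 − 2)/(20 + 2) = 18/22 = 81.8% for k = 21.
6. If item d is coded by its meaning, the ratio is 1 whatever r is.

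The baseline offset is not a measure of bias. Under coding by heading, a caregiver with the safest answer on every item would score 36 of 39 on the 2.1 items (60 of 63 overall). Those 3 points are lost equally in both arms, so they do not by themselves shift the comparison between arms.

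**The case against.** The strongest reply is that Table 1 is a list of survey items and not a scoring key. A journal article may leave scoring to the full protocol or the analysis plan, and the items are said to come from published, validated sources that may well score this one by its meaning. The list is also provisional, since a pilot with 60 caregivers precedes the final questionnaire. The item may simply have been placed near the other road items (a, b and e) by topic.

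Much of this stands. A reader might infer from the table that the supervision outcome does score improvement on this item as harm, and is therefore biased against the intervention. The article does not support that, because it gives no scoring rule. A reader might also infer that the risky sublist loses internal consistency. Nothing in the article says that 2.1 is analysed as a separate scale or that its reliability is assessed. Nor does the article say that the app teaches looking both ways; it names road traffic injury only as a topic.

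The reply does not remove the error. The point is not that a scoring rule is missing but that the article labels a safe behaviour as risky, which is wrong under any scoring. Grouping by topic does not explain it, because the headings sort by direction and a safe road item, the use of child restraints, stands in 2.2. The pilot is an opportunity to correct the list, but as described it covers completion of the questionnaire and user experience, with no mention of checking item direction.

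**Conclusion.** The misplacement is certain: a precaution is item d of a 13-item list of risky behaviours. Its consequence is conditional. If items are coded by their Table 1 heading, more frequent safe behaviour on this item counts as worse supervision. With equal-weight 0–3 coding, no not-applicable answers and equal improvement on all items, a true change would then appear at 84.6% of its size on the 2.1 items, or 90.5% on all 21 behaviour items. That is modest attenuation, not a reversal of the result. If the item is coded by meaning, there is no numerical effect and only the published table needs correcting.

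The reach is one item of one of three secondary outcomes. The primary outcome, the sample size and the primary analysis are untouched. It should still be corrected, because the table as printed gives the wrong direction and the remedy costs almost nothing.

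**What to change.** Move item d from the risky to the safe behaviour sublist when the questionnaire is finalised after the pilot, giving 12 risky and 9 safe items, and record the coding direction of each item alongside the list. If data have already been collected, leave the question as asked and code it as a safe behaviour in the analysis, after confirming that the wording caregivers saw was the positive form printed here.

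Moving the item is better than rewording it in the negative. On this frequency scale, a negative item would make the safe answer a double negative, and it would alter an item that the article presents as validated.

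The cost is one table row, or one line of recoding if data are in hand. No change to design, sample size or data collection is needed.
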